### Analysis

In our analysis, we will be addressing several key indicators such as (1) monitoring the recruitment rate by tracking the number of eligible participants approached versus the number enrolled in the study; (2) tracking the retention and attendance rates of both parents and children; (3) evaluating whether each session’s objectives are met, the content is delivered within the allotted time, and the necessary resources (eg, facilitators and materials) are available; and (4) gathering qualitative and quantitative feedback from participants through postprogram surveys and individual interviews with both children and parents. By assessing these criteria, we will determine if the program and recruitment processes are feasible and ready for expansion into a larger, quasi-experimental study. In order to capture the participants’ experience of the program, semistructured interviews will be conducted and analyzed using thematic analysis [38]. For the statistical analysis, we will use 2-tailed paired sample *t* tests to address potential differences in pre- and postprogram measures. However, if data are not normally distributed, a nonparametric Wilcoxon signed rank test will be used. After each session, group leaders together with the project owner will assess compliance and pay particular attention to any adverse events such as deterioration in family relationships or increasing ill health of the participants. What constitutes an adverse event in psychotherapy can be difficult to define [39], although it could constitute severe illness, parental divorce, etc. We will, therefore, pay particular attention to any of the changes within the individuals and their families in the various parts of the data collection.

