### Measures

The following data will be collected within the framework of this pilot study. The usability of the scales will be evaluated in future analyses. The data given below will be collected from the children:

SCREENS-Q screening form, for valuing children and adolescent’s screen time (adapted version, including questions targeting extent, type of activity, boundary setting, and positive and negative consequences of the child’s screen use): It has shown good internal consistency (Cronbach α 0.61-0.90) [30].Game Addiction Scale for adolescents, for the diagnosis of computer game addiction targeting questions in accordance with the proposedDiagnostic and Statistical Manual of Mental Disorderscriteria for IGD [5]: The instrument has shown good internal consistency (Cronbach α 0.81-0.86) [31].The Kessler Psychological Distress Scale (Kessler-6) screening for depression and anxiety over the past 6 months, including questions regarding feelings of hopelessness and nervousness: It is a widely internationally used measure of psychological distress. The instrument has shown a sensitivity of 0.36 (0.08) and a specificity of 0.96 (0.02) in predicting severe mental illness in a general population [32,33].Parenting Children and Adolescents Scale (PARCA) for assessing aspects of the parent-child relationship and parenting practices (adapted version including questions regarding encouraging positive behaviors and setting boundaries) [34]: This is originally a 19-item measure with each item rated on a 5-point scale. The instrument includes 3 subscales: encouragement of positive behaviors, setting limits, and proactive parenting behaviors, and has shown good psychometric properties (Cronbach α 0.86-0.91) [34].Adult-Child Relationship Scale—Family Check-Up (FCU): It measures warmth and conflict with 8 items rated on a 5-point scale targeting questions such as the tendency to involve parents in the child’s thoughts and feelings and 3 items measure parent-child conflicts and conflict behaviors. Scale α values in previous studies have shown good internal consistency (Cronbach α 0.74-0.85) [35].The Insomnia Severity Index Adolescent for assessing sleep problems: It is a well-established tool for measuring sleep problems in adolescents, including questions targeting the child’s perception of the consequences of their sleep patterns. Scale α values in previous studies have shown good internal consistency (Cronbach α 0.83) [36,37].Background data: gender, age, length, weight, family constellation, parental education level, and diagnosis at CAP.

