
Baseline data that will be collected from the parents before treatment are:

SCREENS-Q screening form for valuing children and adolescents’ screen time (adapted version, including questions targeting extent, type of activity, boundary setting, and positive and negative consequences of the child’s screen use) [30].PARCA for assessing aspects of the parent-child relationship and parenting practices (adapted version including questions regarding encouraging positive behaviors and setting boundaries) [34].FCU: 5 items measure parent-child warmth such as questions about the parent’s perception of the child’s openness about their thoughts and feelings, and 3 items measure parent-child conflicts and conflict behaviors [35].

Given our expectation that a larger evaluation will be able to determine whether the intervention has any impact on screen-related conflicts within families, we will pay particular attention to the usability of the PARCA and FCU instruments. The follow-up data will be collected in connection with the last session of the program. Interviews with children and parents will be conducted approximately 2 weeks after the end of the program. The interviews will focus on the participant’s experience of the program. The quantitative data will be analyzed with SPSS (IBM Corp), and the interview data will be analyzed with thematic analysis [38].

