### Ethical Considerations

The study was reviewed and approved by the Swedish Ethical Review Authority (2023-05533-01; November 13, 2023). The study has been registered at ClinicalTrials.gov (NCT06098807) and approved on October 23, 2023. We have calculated that the risk for patients to participate in the study is low. Mental illness among young people causes great distress and costs both on individual and societal levels. The knowledge and understanding of mental illness among young people are low in general society and particularly low regarding screen behaviors among youth. Hence, new knowledge about treatment of excessive screen use is of uttermost importance and the benefits will be greater than the risks of this project. The trial intervention is similar to other clinical practices offered in child and youth psychiatric clinics, which is why we consider the risks with the trial as minimal. Participants will not receive any economic compensation for their participation in the study. After eligibility is confirmed, written and verbal information about the study will be provided to all participants according to the Swedish Act concerning the Ethical Review of Research Involving Humans (SFS 2003:460). All patients and their carers who verbally agree to take part in the project will be provided with a consent form enabling them to provide written consent. According to Swedish law on research ethics, for patients younger than 15 years of age, written consent from a parent or guardian is also required for their children to participate in the study. All participants will be informed that their partaking in the study is voluntary; their data will be handled with strict confidentiality; results will be reported solely on a group level, which means that individual participants will not be identifiable; and that they are free to withdraw from the study at any time without reporting a reason for withdrawal. Personal and identifiable data will be collected from patients. Data will be kept confidential and managed in accordance with the Data Protection Act, General Data Protection Regulation policies, and the Swedish Act concerning the Ethical Review of Research Involving Humans (SFS 2003:460). Data will be held on services located within the Region Skåne databases, stored and secured both physically (in locked cabinets designed for the purpose) and electronically (behind firewalls), and be accessible to the research team only.

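### The one named adverse-event check is a session-based judgment by those running the program, with no direct harm question or count of individual worsening behind it, so harms may be undercounted

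*Protocol article*

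**What the plan says.** The Analysis section of the protocol article describes two routes by which harm could come to light.

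The first is the only one named as an adverse-event check. After each session, "group leaders together with the project owner will assess compliance and pay particular attention to any adverse events", with examples: "such as deterioration in family relationships or increasing ill health of the participants". The definition is left open: "What constitutes an adverse event in psychotherapy can be difficult to define [39], although it could constitute severe illness, parental divorce, etc".

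The second is more general. The team will "pay particular attention to any of the changes within the individuals and their families in the various parts of the data collection". The Measures section shows what this could draw on:

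- From children and parents: the Family Check-Up (FCU) scale, where "3 items measure parent-child conflicts and conflict behaviors", and the PARCA parenting scale.
- From children only: the Insomnia Severity Index and the Kessler-6, the latter "screening for depression and anxiety over the past 6 months".
- From both: interviews about 2 weeks after the program, directed at how participants experienced it.

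Follow-up questionnaires are collected around the final session. The stated quantitative analysis is a two-tailed paired t test, or a Wilcoxon signed rank test if the data are not normal. Attendance and retention are tracked. Under Ethical Considerations, participants may withdraw without giving a reason. The Enrollment section plans 10 families; the Results section reports 11 children and their parents enrolled, with the sessions delivered in the first quarter of 2024.

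**The concern.** The named check depends on what group leaders and the project owner notice or are told. They deliver and run the program, so they are not disinterested observers. The harms given as examples, worse family relationships and worse health, arise largely at home. A check tied to a session says least about a family that was not there, and a family may be absent because things got worse.

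The second route could make up for this, but nothing stated turns it into a finding about harm. A group-level test answers whether the average moved. It does not show whether one or two children deteriorated while the others improved, and in 10 or 11 families that is the form harm would most likely take.

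This is a first trial of a new program in child psychiatry patients, and its conclusions are to be the foundation for a larger quasi-experimental study. An undercount of harms here would be carried into that study's planning.

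**Working it through.** The article states no harm rate or event figure, so there is nothing to reproduce. The check has four steps.

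**1. What each source of information can show**

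| Source | Who and when | Limit as a harm signal |
|---|---|---|
| After-session judgment | Group leaders and project owner, each session | Open definition; no stated question to families; absent families not seen |
| FCU conflict items | Child and parent, baseline and final session | Families who left are the likeliest to lack follow-up |
| Insomnia Severity Index | Child, baseline and final session | Same |
| Kessler-6 | Child, baseline and final session | Same, and a 6-month recall window |
| Interviews | Child and parent, about 2 weeks after | No harm question stated |

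This assumes that the baseline scales are repeated at follow-up, as the paired tests imply. Enrollment and delivery fell within one quarter, at most 3 months. At follow-up, at least 6 − 3 = 3 months of the Kessler-6 window therefore precede the program.

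**2. Averages against individuals (invented example)**

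Suppose eight children improve by 2 points and two worsen by 4. The mean change is (8 × 2 − 2 × 4) / 10 = 0.8 points of improvement. A two-tailed test allows for a group shift in either direction, but the two children who worsened do not appear in it.

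**3. What zero events would mean**

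The exact two-sided 95% upper limit for 0 of n is 1 − 0.025^(1/n).

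- n = 10: 1 − 0.025^(1/10) = 0.308
- n = 11: 1 − 0.025^(1/11) = 0.285

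**4. What incomplete detection adds**

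Let p be the true share of families harmed and s the share of those harms that is noticed. The chance of recording none is (1 − p·s)^n. All values of p and s are assumptions; the article gives neither.

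| p | s | n = 10 | n = 11 |
|---|---|---|---|
| 5% | 100% | 0.60 | 0.57 |
| 5% | 50% | 0.78 | 0.76 |
| 10% | 100% | 0.35 | 0.31 |
| 10% | 50% | 0.60 | 0.57 |
| 20% | 100% | 0.11 | 0.09 |
| 20% | 50% | 0.35 | 0.31 |
| 20% | 30% | 0.54 | 0.51 |

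For example, at p = 20%, s = 50% and n = 10, (1 − 0.10)^10 = 0.349. With these inputs, halving detection raises the chance of a clean record from about one in ten to about one in three.

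**The case against.** The strongest reply has four parts.

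**There is a second route.** A reader might infer that harms can be found only through what staff notice. The text does not support that. The Analysis section extends attention to all the data collection, which includes families' own reports on conflict, sleep and distress, and interviews. This stands, and it is why the point concerns the strength of ascertainment and not its absence.

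**Harm at home is not necessarily missed.** The sessions deal with conflict triggers, and a parent or child can raise trouble in a separate group. Attendance is tracked, and nothing says that families who left are excluded from interviews. This also stands: the documents support possible undercounting, not a certain loss.

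**No safety claim is planned.** A reader might infer that the pilot is set up to confirm the statement that "we consider the risks with the trial as minimal". That statement is an advance ethical judgment based on similarity to existing clinical practice. Nothing says that the pilot will test it, and the Limitations section calls the study primarily exploratory. The caution about zero events therefore concerns how the result may be read later.

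**This is a condensed article.** Adverse-event forms, detailed definitions and procedures for absent families may stand in the full protocol. That is fair, and the open definition alone is no error; the authors acknowledge it with "What constitutes an adverse event in psychotherapy can be difficult to define". But the article does state who looks, when, and which tests are used, and that stated method can be improved.

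On the arithmetic, the upper limit for zero events reflects sample size and would be the same with perfect detection, so it does not measure the weakness of the check. The detection table does address detection, but it rests on assumed values and gives no separate credit to the scales or interviews.

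**Conclusion.** The concern holds as a risk of undercounting. The one named adverse-event check is a judgment tied to sessions and made by those running the program. The broader promise has no stated harm question and no count of individual worsening behind it. The gap is likeliest for families who miss sessions or leave, because follow-up scales are tied to the final session and withdrawal needs no reason.

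The size of any undercount cannot be derived from the article. What can be derived without assuming a harm rate or a detection share is that zero events would remain compatible with a true per-family rate of up to 31% (10 families) or 28% (11 families), treating families as independent. The full protocol, which is not at hand, may already answer part of this. The change is worth making because it is cheap and the pilot feeds a larger study.

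**What to change.** **1. Ask directly.** In the 2-week interview, ask every child and every parent the same short question about worsening at home or in health. Put it by phone to families who were absent or left, while respecting their right to give no reason. The sessions have already been delivered, so asking at each session can serve only the larger study. If the pilot interviews are also complete, the interview question moves there too.

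**2. Count individuals.** Beside the mean change, report how many children worsened on FCU conflict, the Insomnia Severity Index and the Kessler-6, and how many parents worsened on FCU conflict. Parents do not complete the sleep or distress scales. Count only worsening beyond a margin fixed in advance from measurement error. Without a margin, and with no true change and symmetric noise without ties, about half of the participants would count as worse on each scale. Note beside the Kessler-6 count that its 6-month window overlaps the pre-program period. State how many enrolled children and parents have no follow-up score, because this count cannot reach them.

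**3. Report with a denominator.** Give events per enrolled family with an exact interval, and draw no safety conclusion from zero events.

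The counts are group-level results, so they fit the confidentiality commitment under Ethical Considerations. The cost is one short question per participant, a few phone calls and one descriptive table. The downside is a little staff time and more minor events recorded.

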### Ethical Considerations

The study was reviewed and approved by the Swedish Ethical Review Authority (2023-05533-01; November 13, 2023). The study has been registered at ClinicalTrials.gov (NCT06098807) and approved on October 23, 2023. We have calculated that the risk for patients to participate in the study is low. Mental illness among young people causes great distress and costs both on individual and societal levels. The knowledge and understanding of mental illness among young people are low in general society and particularly low regarding screen behaviors among youth. Hence, new knowledge about treatment of excessive screen use is of uttermost importance and the benefits will be greater than the risks of this project. The trial intervention is similar to other clinical practices offered in child and youth psychiatric clinics, which is why we consider the risks with the trial as minimal. Participants will not receive any economic compensation for their participation in the study. After eligibility is confirmed, written and verbal information about the study will be provided to all participants according to the Swedish Act concerning the Ethical Review of Research Involving Humans (SFS 2003:460). All patients and their carers who verbally agree to take part in the project will be provided with a consent form enabling them to provide written consent. According to Swedish law on research ethics, for patients younger than 15 years of age, written consent from a parent or guardian is also required for their children to participate in the study. All participants will be informed that their partaking in the study is voluntary; their data will be handled with strict confidentiality; results will be reported solely on a group level, which means that individual participants will not be identifiable; and that they are free to withdraw from the study at any time without reporting a reason for withdrawal. Personal and identifiable data will be collected from patients. Data will be kept confidential and managed in accordance with the Data Protection Act, General Data Protection Regulation policies, and the Swedish Act concerning the Ethical Review of Research Involving Humans (SFS 2003:460). Data will be held on services located within the Region Skåne databases, stored and secured both physically (in locked cabinets designed for the purpose) and electronically (behind firewalls), and be accessible to the research team only.

## Results

A total of 11 children and their parents were enrolled during the first quarter of 2024. A 4-session pilot was delivered in the first quarter 2024, and the first results are expected in the third quarter 2024. The results are intended for publication in international peer-reviewed scientific journals and presentation at international and national scientific conferences. A primary publication is planned for the first quater of 2025. Additional secondary publications may follow. Whenever possible, the results will be presented in open-access journals.

## Discussion

### Expected Outcomes

This study aims to evaluate the delivery and feasibility of the newly developed family-centered group program (FAME) designed to address problematic gaming and excessive screen use among children and adolescents aged 10-18 years within a CAP setting. The program is based on established empirical knowledge in the field (Textbox 1) and our own experiences from previously completed studies [18,40,41]. We anticipate that (1) the program will demonstrate feasibility in terms of treatment delivery and participant recruitment, (2) participants’ experiences with the program will provide valuable insights for further development and testing, and (3) the selected measurement instruments will be relevant and effective in evaluating program outcomes.

Our intention is that both the quantitative and the qualitative exploration of the pilot study will form an important basis for refining the program, as well as for the development of a larger study. Based on the low number of participants, it will not be possible for us to draw any conclusions regarding the program’s effect. However, we expect to observe a decrease in children’s problematic screen use, including a reduction in the amount of time spent using screens. Additionally, we anticipate improvements in the parent-child relationship, characterized by reduced conflict and increased family cohesion. If these criteria are met, we will consider modifying the program as needed and proceed to a fully powered study.

Despite the huge interest in children and adolescents’ screen behavior in both popular science and more clinical and scientific contexts, to date, there is neither consensus regarding what is acceptable screen time nor evaluated family interventions for problem gaming and excessive screen use. Child screen use is generally seen as both a cause and a consequence of problematic parent-child relationships [42,43], and family interventions, where both the child and the parents are included, are both recommended [24] and requested [40]. Therefore, this would be the first intervention of a kind that could be of help to both children and their parents. Such an intervention could be beneficial for individual families, but it could also be an effort that would contribute to reduced health inequalities among children and families.

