### Enrollment

Primary care patients (*Första linjen*) seeking treatment at CAP units in Skåne for problematic gaming or excessive screen time will be given the opportunity to participate in our treatment program. Patients contact CAP Skåne through En Väg In, a call center managed by psychiatry nurses and health care counselors. During the standard intake interview, patients are asked “Does your child (or “do you” if the child calls themselves) have any problems related to gaming or screen use?” As part of the existing procedure, parents or children who call En Väg In are also asked if they consent to be contacted for participation in research programs. The responses are tagged by the staff, and these tags are analyzed weekly by research administrators. Families with both tags are then contacted and provided with oral and written information about the study and the program. Families can be included in the study in 2 ways: either by being contacted by the research team during the initial contact with CAP, following the procedure described above, or by their therapist at CAP. Therapists at CAP can contact the study if families have described screen-related family conflicts in the context of receiving other care and have consented to be contacted by the research team for further information about the study. Regardless of the contact method used, research team staff will contact guardians by phone in an initial call to provide information about the study, assess motivation and consent, and verify inclusion and exclusion criteria. If all inclusion criteria are met and no exclusion criteria are present, the family will be scheduled for session 0, the content of which has been described above. For this pilot study, we will enroll 10 families, involving both the child and parent or parents. The inclusion and exclusion criteria are provided in Textbox 2.

Inclusion and exclusion criteria.

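### The article states two different conditions for moving to the larger study, and one of them is pre-post improvement that its own text says cannot show an effect

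*Protocol article*

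**What the plan says.** The protocol article describes progression in two places.

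- **Methods, Analysis.** Four indicators are listed: recruitment rate, retention and attendance of parents and children, session delivery (objectives, time, resources), and participant feedback. Then: "By assessing these criteria, we will determine if the program and recruitment processes are feasible and ready for expansion into a larger, quasi-experimental study".
- **Discussion, Expected Outcomes.** The authors say that because of the low numbers "it will not be possible for us to draw any conclusions" on the program's effect. They go on to expect less problematic screen use and less screen time, and a better parent-child relationship marked by "reduced conflict and increased family cohesion". The next sentence is: "If these criteria are met, we will consider modifying the program as needed and proceed to a fully powered study".

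On design, the Enrollment section states "For this pilot study, we will enroll 10 families, involving both the child and parent or parents", and the Results section reports that "A total of 11 children and their parents were enrolled during the first quarter of 2024". The Analysis section specifies paired t tests, or Wilcoxon signed rank tests, as "tests to address potential differences in pre- and postprogram measures". No control group is described. The Measures section says: "The follow-up data will be collected in connection with the last session of the program". One inclusion criterion is that the family reports problems with gaming or screen use.

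**The concern.** Whether to go on to a larger study is the main decision this pilot informs, and the article states two bases for it. If attendance and delivery are good but scores are flat, the Analysis section points to expansion and the Expected Outcomes sentence does not. If scores improve but recruitment or delivery is poor, the two point the other way round.

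The improvement condition also relies on data that its own paragraph sets aside as evidence of effect. Families are recruited when a problem is being reported, so some decline by the last session can be expected from regression to the mean alone, and there is no comparison group to separate that from a program effect. A program that does nothing could meet the condition.

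**Working it through.** **1. The two statements side by side**

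| | Analysis | Expected Outcomes |
|---|---|---|
| What is judged | Recruitment; retention and attendance; delivery; feedback | Problematic screen use; screen time; conflict; family cohesion |
| Kind of evidence | Feasibility | Pre-post change in one group |
| What follows | Ready for a larger quasi-experimental study | Modify as needed and proceed to a fully powered study |

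Both places use the phrase *these criteria*, but nothing in the first list appears in the second. In Expected Outcomes the nearest antecedent is the pair of sentences on expected improvement.

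**2. How easily the improvement condition is met without an effect**

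The article gives no effect size, SD, correlation or error rate, so it has no figure of its own to reproduce. The following is illustrative.

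Inputs:
- n = 10 families (Enrollment); 11 enrolled (Results).
- Assumed: pre-post correlation r = 0.7.
- Assumed: families enter z = 0.5 to 1.0 SD above their usual level.
- Assumed: correlation among the four outcome changes rho = 0.3 to 0.5.
- Assumed: the condition is met when the mean change is in the favourable direction, since the article sets no size.

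Formulas, in SD units, with no program effect:
- Expected drop = z(1 - r): 0.5 × 0.3 = 0.15; 1.0 × 0.3 = 0.30.
- SD of change = √(2(1 - r)) = √0.6 = 0.775.
- Standard error at n = 10 = 0.775/√10 = 0.245.
- P(mean moves favourably) = Φ(drop/SE): Φ(0.15/0.245) = Φ(0.61) = 0.73; Φ(0.30/0.245) = Φ(1.22) = 0.89.
- At n = 11 the same steps give 0.74 and 0.90.

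Probability that all four means move favourably at n = 10, by simulation from a multivariate normal with the same shift on each outcome:

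| Entry level | rho 0.3 | rho 0.5 |
|---|---|---|
| z = 0.5 | 0.38 | 0.45 |
| z = 1.0 | 0.68 | 0.72 |

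Without any regression to the mean, the all-four probabilities would be 0.14 and 0.20. Most of the chance of a false pass therefore comes from how families enter the study.

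Widening the assumptions to r = 0.6 to 0.8 and z = 0.5 to 1.5 moves the single-outcome probability at n = 10 to between 0.69 and 0.98.

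**3. Cohesion**

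The Measures section describes the Family Check-Up scale as covering warmth and conflict, and PARCA as covering parenting practices and aspects of the parent-child relationship. No listed instrument is said to measure family cohesion by name.

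**The case against.** The strongest reply is that the Analysis section, in Methods, is the operative text. It ties readiness to feasibility, in line with the abstract, the stated objective, and the Limitations section, which puts implementation ahead of efficacy. The Expected Outcomes sentence sits in the Discussion, is hedged, and could reach back to the three anticipations in the paragraph before it (feasibility, experiences, instruments). This stands in part: improvement is one stated condition, not the whole basis of the decision. It does not remove the conflict, because the plain reading of the sentence still includes the improvements.

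Three stronger readings are tempting, and the document does not support them.

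- A reader might infer that the decision to proceed rests on noise alone. The Analysis section rules that out.
- A reader might infer that a useful program would often be stopped by chance. With a true change of 0.3 SD of change on each outcome and no regression to the mean, all four means move favourably only 55-60% of the time, a miss of 40-45%. But the article has no stop rule and does not require all four. That figure also leaves out the regression to the mean on which the false-pass figures depend. With it kept in (r = 0.7, z = 0.5 to 1.0), all four move favourably about 81-95% of the time, so the miss falls to about 5-19%.
- A reader might count the absence of numerical progression cut-offs as a fault. A condensed article may leave these to the full protocol, which is not shown.

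The cohesion point is also minor: the word describes the parent-child relationship in loose terms, and that relationship is measured.

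**Conclusion.** The point holds as a conflict between two stated bases for progression, one of which the article itself disqualifies as evidence of effect. That conclusion needs no assumptions beyond the plain reading of *these criteria*.

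The size of the bias is illustrative. With no program effect, a single outcome would look favourable about 73-89% of the time at 10 families, and all four about 38-72% of the time. These figures depend on the assumed r, z and rho and on a direction-of-mean rule that the article does not state. Regression to the mean is inferred from problem-based entry and the lack of a control group; the article does not quantify it. No sample-size figure changes.

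**What to change.** Reword the progression sentence in Expected Outcomes so that moving to the larger study rests on the four feasibility indicators in the Analysis section. Add that pre-post changes are reported descriptively and are not a condition for proceeding. If family cohesion stays as an expected outcome, link it to a listed instrument, for example the warmth items of the Family Check-Up scale; otherwise drop the term.

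This is a change of one or two sentences and needs no new data or analysis. The authors would no longer be able to cite score improvement as a ground for going ahead.
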